#### D.2.3. Measurement of Potential Confounders

Randomization is expected to ensure comparability of the groups for most maternal and infant characteristics that may influence the key outcomes. However, this needs to be assessed, and controlled for appropriately especially if there are differences. Data will therefore be collected on the following maternal and infant characteristics.

D.2.3.1. Sociodemographic Characteristics and Obstetric History: Data on maternal sociodemographic characteristics and obstetric history will be collected using questionnaires that have been used in previous studies by the study investigators. The instrument used by [name] (see Appendix *III*) has been validated for use in pregnant women from low-medium socioeconomic status at the National Institute of Perinatology in Mexico. It contains 55 questions that can be administered by a nurse or social worker and takes approximately 20-25 minutes. The first section includes questions regarding marital status, place of birth, years of schooling, occupation, household income and composition. The second section includes questions about reproductive history, like number of pregnancies, number of abortions, causes, number of live children, number of death children and causes, previous and current pregnancy complications like: hypertension, convulsions, bleeding, etc. The third section contains questions about nervous sicknesses, depression, psychiatric disorders, and addictions like smoking, drug and alcohol use.

D.2.3.2. Maternal pre-pregnant nutritional status: Maternal prepregnant nutritional status especially fat stores may influence the outcomes of interest. Prepregnant weight (wt) and height (ht) will be determined from hospital records and body mass index (BMI) will be calculated (BMI = wt in kg /(ht in m)2) Since many women access prenatal care early, the measurements at the first prenatal visit will be used.

D.2.3.3. Maternal Diet *(revised): A 24-hour recall survey protocol that has been used and validated in previous studies in Guatemala and Mexico[[214]](#endnote-214) (see Appendix III) will be used to estimate and compare mean intakes of macronutrients (energy (kcal), fat (g, % of total energy), protein (g, % of total energy), carbohydrate (g, % of total energy), total monounsaturated acids (g, % of total energy), total PUFA (g, % of total energy), total saturated fatty acids (g, % of total energy), total EFA (g, % of total energy), total n-3 PUFA (g, % of total energy), and individual fatty acids(ALA (g), LA (g), AA (mg), EPA (mg), DPA (mg), and DHA (mg)) in the two groups. Patterns of consumption of DHA rich foods will also be compared. A single 24-hour dietary recall will be administered at recruitment (20-24 wks gestation) and at 3 and 6 months postpartum by trained nurses at the study headquarters. The period of recall will be for the day before the interview beginning at 6 am and ending at 6 am on the day of the interview. The administration of this instrument takes approximately 30 minutes. The multipass method will be followed. The 3 passes will include (1) an overview of the days activities and eating occasions; (2) a detailed inventory of foods eaten at each occasion; and (3) a review and set of probes to ascertain any additional food items that may have been omitted. Local cooking and serving utensils and a kitchen scale will be used to assist in the estimation of portion size and details of recipes will be obtained. The amounts of food ingested will be recorded in grams. Data entry and conversions from food items to nutrient values will be done using a compilation of food composition tables for Latin American foods and extensively tested computer programs developed at INSP. The food composition tables include values obtained from INSP, INCAP and the United States Department of Agriculture[[215]](#endnote-215).*

D.2.3.4. Maternal Intelligence: Maternal cognitive functioning can influence infant development, as the mother is typically the primary caregiver during the early years. We will therefore assess her cognitive functioning at recruitment using Raven’s Progressive Matrices, a nonverbal test of intellectual functioning which requires the participant to figure out complementary abstract patterns[[216]](#endnote-216). The Raven’s test has been shown to be a useful measure of generalized intelligence, especially in low literacy societies and has been used by the investigators in previous studies in Guatemala and Mexico. The test measures the ability to form comparisons, reason by analogy, and to organize spatial perceptions into systematically related wholes. The Standard Progressive Matrices form, which contains 60 items presented in five sets (12 items per set), will be used. Raw scores will be converted into percentile ranks. The test takes between 15 and 30 minutes and will be administered by trained psychologists[[217]](#endnote-217).

D.2 3.5. Home Environment: Aspects of the home environment have been shown to be strongly associated with cognitive and language development[[218]](#endnote-218),[[219]](#endnote-219). In order to control for these potential influences when examining the effects of DHA supplementation on child growth and development, the HOME Inventory, a measure of the home environment that is widely used, will be employed[[220]](#endnote-220). The HOME Inventory assesses the quality and quantity of social, emotional, and cognitive support available to a child in the home environment, and is composed of six subscales: parental responsivity, acceptance of child, organization of the environment, provision of appropriate materials, parental involvement, and variety of stimulation. Several reviews have suggested that this inventory is a reliable and valid measure of the home environment and that it is related in expected ways to several health and development measures, as well as to many ecological factors[[221]](#endnote-221),[[222]](#endnote-222). This inventory will be completed in the home by trained social workers at 6 and 12 months of age and will take approximately one hour to complete. *A reduced version of the scale will be administered by the social workers during the hospital visit at 18 months of age primarily to capture any major changes in the home environment since the last visit and will take ~ 20-30 minutes.*

D.2.3.6. Infant Diet *(revised)* : Since breastfeeding is associated with neurodevelopmental outcomes in infants[[223]](#endnote-223) and the duration of breastfeeding cannot be controlled by study design, the duration of breastfeeding will be controlled in the data analysis. *Feeding practices and dietary intakes will be assessed using a structured 24 hour recall survey (Appendix III) by trained nurses at the time the infant visits the hospital.* Exclusive breast-feeding will be defined in accordance with the WHO[[224]](#endnote-224) definition (the infant receives breast milk only with no other liquids or solids). Predominant breast-feeding will be defined as receiving breast milk plus fluids (e.g., water, juices) and less than 2 fluid ounces of any commercial infant formula per day. *Administration of the 24-hour recall and calculation of energy and nutrient intakes will follow protocols similar to that described under maternal diet.*

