Dietary changes during pregnancy and early childhood may therefore lead to changes in the composition of cell membranes and organelles in the brain, which in turn may modify brain function through changes in cell growth, cell division, enzyme activity and distortion of cellular cytoarchitecture. There is also evidence that the effects of DHA may also be mediated by **modulating gene expression** in the developing retina and brainError: Reference source not found. Intracellular fatty acids or their metabolites regulate transcriptional activation of gene expression during adipocyte differentiation and retinal and nervous development. DHA also has significant effects on the functional maturation of the central nervous system. These findings clearly call for more studies that examine the role of improving maternal dietary intakes during pregnancy on later neurodevelopmental outcomes, especially in settings where intakes are deficient and growth and development are sub-optimal. In summary, there is strong justification for the trial we propose. The impact of DHA supplementation during pregnancy on early childhood growth and development is hypothesized to be mediated through its direct effects on growth and development during the prenatal period and indirectly via quantity and quality of PUFA stores at birth as well as the availability in breast-milk during early childhood.

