**D.4.1. Overview of Statistical Approach**:

Generally, we will analyze outcomes from birth to 12 months of age among all children who reach that time point. In further analyses to be conducted in the subsample of children who are followed up until 18 months of age, missing interim endpoints will be imputed using multiple imputation procedures as described by Little and Rubin[[228]](#endnote-228). Effectiveness of randomization will be examined by comparing the two groups on key baseline characteristics. In the case of significant differences, group differences in outcomes will be examined with and without adjusting for these factors. Loss to follow-up is expected to be 20% to 18 months. We will assess selection bias by comparing baseline characteristics of subjects with and without the outcome measure of interest and control for any observed differences in the analyses.

All statistical analysis will be done using Statistical Analysis Software (SAS)[[229]](#endnote-229). A probability of p<0.05 will be considered statistically significant for all hypothesis testing. Assumptions of normality will be assessed using plots and tests of normality. Non-normal variables will be transformed or categorized as required. Descriptive data analysis will include examining the distributions of neurodevelopment, dietary intakes, anthropometric and PUFA status. Means, standard deviations, quartiles and median levels will be reported. Individual analytical hypotheses will be tested using the following general statistical techniques:

D.4.1.1. Outcomes measured at one time point: These are analyses which model outcomes collected at one point in time as a function of variables collected either cross-sectionally or longitudinally. For example, cognitive development at 18 months may be modeled as function of prenatal and postnatal growth, diet, and social confounding factors. These analyses can take several forms.

i. Analysis of Covariance will be used for comparison of means of two or more categories (e.g. supplement groups) adjusting for covariates, which may be either continuous or categorical.

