ii. General linear models based on least squares fit will be used when the dependent outcomes are continuous variables such as indicators of child growth and development and nutrient intakes. Independent variables can include continuous, categorical and dummy (0/1) variables. Two approaches, Ordinary Least Squares (OLS) regression and Two Stage Least Squares (2SLS) will be used, depending on the issues addressed.

iii. Logistic regression may be used if the response variable is dichotomous (e.g. stunting defined as ht/age Z score <= -2 ). Adjusted odds ratios will be calculated to estimate risk for the independent variable of interest namely supplement use while controlling for other confounding variables.

D.4.1.2. Outcomes measured on repeated occasions: Some of the data are obtained from repeated measurements on individuals over time (e.g. length measurements at birth, 1, 3, 6, 9, 12, and 18 months of age). Such longitudinal data are very useful for describing dynamic processes which would be poorly captured by a single outcome or "point prevalence" assessment. Independent variables can also be time varying (e.g. feeding practices by time period: 0-3, 3-6, 6-9, 9-12 and 12-18 months) or fixed (e.g. household SES). Examples of the variables we will be modeling longitudinally include:

- **Child outcomes:** birth size, growth, motor and mental development
- **Determinants of interest:** Supplement group
- **Controlling for confounding variables:** SES, maternal BMI, intelligence, home environment.

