The analytic complexities that are introduced by this approach can be addressed using methods that have been developed recently for handling longitudinal/repeated measures data, namely Generalized Estimating Equations (GEE) approach and mixed models. The GEE approach is useful for analyzing either discrete or continuous longitudinal data and accounts for the correlation among repeated measures in the calculation of both parameter and variance estimates[[230]](#endnote-230),[[231]](#endnote-231). Additionally, it is able to accommodate time‑dependent as well as time‑independent covariates. For analyses in which the response variable is continuous and the assumption of multivariate normality is met, an alternate approach is to do mixed model analyses, using, for example, the SAS procedure PROC MIXED[[232]](#endnote-232). This procedure allows the inclusion of both fixed and random effects and, in repeated-measures situations, is more flexible and widely-applicable than standard univariate or multivariate approaches.

D.4.1.3. Structural Equation Modeling (SEM): Structural equation modeling (also known as path analysis and simultaneous equation systems) is an advanced multivariate technique widely used for testing causal models in behavioral and social research[[233]](#endnote-233),[[234]](#endnote-234). This approach will be used to test the significance of the various pathways proposed in the conceptual framework (Figure 1) accounting for the covariance within the different constructs. SEM is also useful to test bi-directional causal relationships (eg: caregiver interaction and motor development) and longitudinal data and can incorporate latent variables. SEM is particularly suited to handle issues of endogeneity inherent in the models to be developed. In order to obtain unbiased estimates, one develops multiple equations to describe the mechanisms of the system, one for each endogenous variable. The simplest and most commonly used technique for the estimation of systems of linear simultaneous equations is the class of instrumental variables estimators [[235]](#endnote-235),[[236]](#endnote-236) of which two-stage least squares (2SLS) is the most important special case. We will use this approach extensively. Recent versions of the appropriate computer packages (eg: AMOS, EQS, PROC CALIS in SAS) for testing complex causal models by SEM will be used[[237]](#endnote-237)*.*

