***Pr {HAZ <= -2 at 18 mo} = Constant + β1 (Supplement)+ β2 (Other confounding)* *+ β3 (Supplement * other confounding)***

The various pathways indicated in the conceptual framework will be tested using techniques described in SEM. For example, 2SLS can be used to model birth weight as a function of supplement group controlling for other confounding, and in turn these estimates will be used to predict attained size at 18 months of age. Similar models will be developed for indicators of neurodevelopment and examine the role of caregiver interaction.

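### Breast-feeding duration and HOME score, both measured after randomisation, are treated as confounders of the supplement effect, and no unadjusted or baseline-only estimate is named as primary

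*Protocol*

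**What the plan says.** **Breast-feeding.** Protocol D.2.3.6 (Infant Diet), within the section on potential confounders, states without condition that "the duration of breastfeeding will be controlled in the data analysis".

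**HOME.** D.2.3.5 explains its purpose: "In order to control for these potential influences when examining the effects of DHA supplementation on child growth and development, the HOME Inventory" will be used. It is scored at 6 and 12 months, with a reduced version at 18 months (D.2.3.5, Table 5). D.4.1.2 then lists the confounders for the longitudinal models, with supplement group as the determinant: "SES, maternal BMI, intelligence, home environment". The first three are available at recruitment; home environment is not.

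**When to adjust.** D.4.2 plans unadjusted t tests for length, weight and biochemical values, and adjusted comparisons only where control of confounding turns out to be needed. It promises every result both before and after adjustment. It does not say which version is the main estimate. E.10 calls child development the primary outcome.

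**Related models.** D.4.1.1 gives as an example that "cognitive development at 18 months may be modeled as function of prenatal and postnatal growth, diet, and social confounding factors". D.4.2 ends with another example: two-stage least squares (2SLS) can model birth weight from supplement group, "and in turn these estimates will be used to predict attained size at 18 months of age". B.6 sets out how DHA is thought to act: directly on prenatal growth and development, and indirectly through fatty-acid stores at birth "as well as the availability in breast-milk during early childhood".

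**The concern.** A confounder of the supplement effect must influence who receives the supplement. Allocation is random and happens before delivery, so nothing measured in infancy can do that. A chance imbalance in a baseline variable is a sound reason to adjust. A difference between groups in breast-feeding or HOME may instead be a result of treatment.

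If it is, adjustment does two things. It removes the part of the DHA effect that runs through the covariate. It also opens a non-causal path wherever an unmeasured factor drives both the covariate and the child's score. The resulting coefficient is neither the effect of assigning DHA nor, without further assumptions, a clean direct effect.

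The stake is interpretation of the 18-month development result. If the two versions differ, the protocol's own terms present the adjusted one as corrected for confounding, although the unadjusted one is the valid estimate of the randomised effect.

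**Working it through.** **1. The plan's own figure.** Inputs from D.1.4 and Table 3: MDI standard deviation 15, difference 3.75, so 0.25 SD; two-sided 5%; 90% power. n per group = 2 × (1.960 + 1.282)² / 0.25² ≈ 337, against 338 stated. Power at 338 is 0.901. The sample size is sound and is not affected by this point.

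**2. What adjustment does, in SD units.** Let a be the DHA effect on the covariate and b the covariate's slope on the outcome. With no shared unmeasured cause:

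adjusted effect = total effect − a × b

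The protocol gives neither a nor b for breast-feeding duration or HOME. The values below are assumptions, with a total effect of 0.25 SD and 338 per group.

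| a | b | Adjusted effect (SD) | MDI points | Share lost | Power |
|---|---|---|---|---|---|
| 0 | 0.1–0.3 | 0.25 | 3.75 | 0% | 0.90–0.93 |
| 0.1 | 0.1–0.3 | 0.24–0.22 | 3.60–3.30 | 4–12% | 0.88–0.85 |
| 0.2 | 0.1–0.3 | 0.23–0.19 | 3.45–2.85 | 8–24% | 0.85–0.74 |

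The first row matters most: if DHA does not move the covariate, there is no bias.

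**3. Adding a shared unmeasured cause.** Let it load g on the covariate and c on the outcome. Then adjusted effect = total − a × (b + c × g). With assumed b = 0.2 and c = g = 0.4, b + c × g = 0.36:

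- a = 0.1: 0.25 − 0.036 = 0.214 (simulated 0.213, power 0.84).
- a = 0.2: 0.25 − 0.072 = 0.178 (simulated 0.178, power 0.69).
- Zero total effect, a = 0.3, b = 0: 0 − 0.3 × 0.16 = −0.048 (simulated −0.049, type I error 0.095 against a nominal 0.05).

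In the same simulations (3,000 per setting) the unadjusted comparison returned 0.249–0.250 SD with power 0.89–0.90, and −0.001 under the null.

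**4. The hypotheses that condition on earlier outcomes.** D.1.1 asks about growth over and above birth size, and about 18-month scores over and above differences at 6 and 12 months. Here the protocol does expect DHA to change the conditioning variable. Take a = 0.25 (Table 3) and use Table 4's repeated-measure correlation of 0.2 as b. Adjusting for one earlier score gives 0.25 − 0.25 × 0.2 = 0.20 SD, or 3.0 points, 20% below the total effect. That is a legitimate direct-effect question, but not the effect of assignment.

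**5. 2SLS through birth weight.** With supplement group as the instrument, the estimate is (β × a + d) / a. Here a = 0.22 SD is the effect on birth weight (Table 3), β is the true birth-weight slope, and d is any effect of DHA on 18-month size by another route. The method needs d = 0, but B.6 names other routes. With assumed β = 0.2:

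- d = 0.05: (0.044 + 0.05) / 0.22 = 0.43.
- d = 0.20: (0.044 + 0.20) / 0.22 = 1.11.

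The error falls on the birth-weight coefficient. The supplement contrast does not change.

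**The case against.** The strongest reply is that D.4.2 reports every result before adjustment as well as after. That stands. A reader might infer that the randomised effect itself will be biased. The documents do not support this, because an unadjusted comparison free of the problem will be shown. A statistical analysis plan, not seen here, may also name the primary estimate. But the protocol itself fixes an unconditional rule for breast-feeding that conflicts with its conditional rule in D.4.2.

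It can also be said that nothing shows DHA alters either covariate. For breast-feeding duration that is fair. Allocation is blinded, all women intend to breast-feed predominantly to 3 months, and the breast-milk route in B.6 concerns the availability of fatty acids in milk, not how long feeding lasts. For HOME, D.4.1.3 mentions two-way influence between caregiver interaction and motor development as something structural models can test. That makes a route from DHA to HOME conceivable, but the protocol does not assert one.

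Three further readings go too far:

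- **Postnatal growth and diet as planned adjustments of the treatment comparison.** The sentence in D.4.1.1 is an optional example and names no supplement term.
- **2SLS as a bias in the DHA effect.** D.4.1.3 does plan extensive use of 2SLS, but the birth-weight model is an optional pathway analysis, and its fault stays in the pathway coefficient.
- **Sizing the bias from the 7-point mental score difference in the preliminary studies.** That difference concerns DHA intake among exclusively breast-fed infants, not longer against shorter breast-feeding.

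**Conclusion.** The concern holds in a limited form. The protocol places two post-randomisation variables in its confounder set, one of them by firm commitment, and does not say whether the adjusted or the unadjusted result is the estimate of the DHA effect. The adjusted estimate equals the effect of assignment only if DHA leaves both variables unchanged.

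The size cannot be determined from the protocol. It is zero with no DHA effect on the covariate. Under the assumed values (shift up to 0.2 SD, slope 0.1 to 0.3) it reaches 24% of the 0.25 SD target, or 0.9 MDI points. It can be larger if covariate and outcome share an unmeasured cause. The unadjusted comparison, the sample size and the power calculation are not affected.

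The 2SLS point is separate and secondary: on the protocol's own pathways the exclusion restriction fails, so the birth-weight coefficient cannot be read as an unbiased causal effect.

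**What to change.** Amend D.2.3.5, D.2.3.6, D.4.1.2 and D.4.2 as follows.

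- Name as primary either the unadjusted comparison or one adjusted only for pre-randomisation variables: SES, maternal BMI and Raven's score. Choose one in advance.
- Remove breast-feeding duration and HOME from the confounder set. Report models that contain them as secondary mediation analyses. This also resolves the conflict between D.2.3.6 and D.4.2.
- Keep the hypotheses that condition on birth size and on 6- and 12-month scores, but label them as direct-effect (mediation) questions.
- Do not present the birth-weight 2SLS estimate as an unbiased causal effect; state that its exclusion restriction conflicts with the pathways in B.6.

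The cost is analysis wording only, since the baseline covariates are already to be collected. The downside is a little precision if HOME is prognostic. With an assumed slope of 0.2, an unmeasured cause as in step 3 and no DHA effect on the covariate, simulated power was 0.94 with the covariate and 0.90 without. SES and Raven's score may recover part of that.
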